### Safety Considerations

Exclusively certified medical products will be used. Blood sampling and tissue biopsies during the transplant procedure will be performed according to clinical standards, preventing any relevant study-related risks or additional burden on the subjects. An interim analysis will be performed as soon as 10 patients are HOPE-treated. The trial will be terminated immediately if the following criteria is fulfilled: significantly higher DGF rate (*P*<.05 using the Chi-squared test) in the HOPE group compared to the matched conventional cold storage group (efficacy).

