### Hypothermic Oxygenated Machine Perfusion Versus Historic Cold Storage Group

Primary and secondary outcomes of patients transplanted with the HOPE-treated kidneys will be compared to a case-matched group of 30 patients (1:2 matching) transplanted with ECD organs after conventional cold storage, using identical surgical techniques and perioperative treatment at the Department of Surgery and Transplantation, University Hospital RWTH Aachen. The present trial comprises two groups, a perfusion (Group 1, HOPE) and a control conventional cold storage group (Group 2, Historic). Patients on the waiting list for kidney transplant with proven written consent will be recruited. HOPE will be applied to the allograft in the operating room after regular organ procurement, transport, and back-table preparation (Figure 1).

We adapted a protocol based on clinical studies with nonoxygenated hypothermic machine perfusion, and on preclinical experience with HOPE [11,18,19]. HOPE will be applied through the renal artery for at least two hours, with a perfusion pressure of 25 mmHg and a perfusion rate of 50-200ml/min using 1 L of recirculated perfusate at 0-4°C. The perfusate will be oxygenated using medical grade oxygen (O^2^), with a partial pressure of oxygen (pO^2^) of 60-80 kilopascals (kPa), by an oxygenator included as a disposable part of the setup. Perfusion parameters registered by the device will be stored automatically and evaluated for possible patterns. Immediately prior to perfusion, grafts will be flushed with perfusate solution to wash out the residual histidine-tryptophan-ketoglutarate (HTK) solution. Storage, management, and use of the medical products will be carried out according to the manufacturer’s guidelines.

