### Study Endpoints

The primary endpoint is DGF, which is defined as the need for dialysis in the first 7-days posttransplantation. The secondary endpoints of the study include: (1) duration of DGF (defined as the period between kidney transplant and last dialysis in days) and functional DGF (defined as <10% fall in serum creatinine for 3 consecutive days in the first week posttransplantation); (2) creatinine reduction ratio day 2 ([creatinine day 1−creatinine day 2]/creatinine day 1) and Creatinine reduction ratio day 5 ([pretransplant creatinine−creatinine day 5]/pretransplant creatinine); (3) incidence of postoperative complications, as assessed by the Clavien-Dindo complication score and the comprehensive complication index [22]; (4) duration of intensive care and hospital stay; (5) recipient and graft survival after six months; (6) renal function (assessed by serum creatinine and eGFR) at one-, three- and six-months post-transplant; and (7) basic and translational research, which involves assessing biomarkers from routinely harvested kidney tissue and serum following implantation to obtain information on kidney injury, extent of oxidative damage, redox- and energetic homeostasis of the implanted donor kidney.

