### Study Population

To the best of our knowledge, aside from a sole case of HOPE-treated dual kidney transplant reported recently, no experience of HOPE in human donation after brain death kidney transplant has been published yet [23]. In the present pilot study, 15 patients (N=15) will be treated with HOPE to gain first prospective clinical knowledge. HOPE-treated patients will be compared to a case matched group of 30 patients (N=30).

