### Data Collection and Statistics

Patients will be given consent forms while in our outpatient clinic. Data will be obtained using study specific CRFs completed by the members of the study team. Subjects will be informed about data protection, including pseudonymization. Encoded data will only be provided to authorized persons (ie, authorized study staff, authorities, institutional review board). The study will be prematurely terminated for any individual subject in case of study-related complications or if the subject withdraws informed consent. Parametric and nonparametric tests will be done according to the normality of the data distribution. Two-way analysis of variance will be used for the time-course analysis of laboratory parameters. The log-rank test will be used for comparisons between Kaplan-Meier curves of six-month graft survival. Statistical significance will be defined as *P*<.05.

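### The one trial-level stopping rule (DGF higher at chi-squared P<.05 after 10 HOPE patients) is insensitive to moderate harm and is triggered before the tenth patient's 7-day endpoint is complete

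*Protocol article*

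**What the plan says.** Under Safety Considerations the protocol article sets one interim look: "An interim analysis will be performed as soon as 10 patients are HOPE-treated". One criterion halts the trial: "The trial will be terminated immediately if the following criteria is fulfilled: significantly higher DGF rate", at P<.05, "using the Chi-squared test) in the HOPE group compared to the matched conventional cold storage group (efficacy". The Data Collection and Statistics section gives the general threshold, "Statistical significance will be defined as *P*<.05", and separately allows an individual subject's participation to end because of complications. That second provision does not halt the trial.

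Under Study Endpoints, DGF is "the need for dialysis in the first 7-days posttransplantation". The Study Population section plans that "15 patients (N=15) will be treated with HOPE to gain first prospective clinical knowledge", and these patients are "compared to a case-matched group of 30 patients (1:2 matching) transplanted with ECD organs after conventional cold storage".

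The article does not state an expected control DGF rate, the sidedness of the interim test, whether a continuity correction applies, whether 20 or 30 controls enter the interim comparison, or how often the rule would stop the trial under any assumed truth.

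**The concern.** A harm rule should be judged mainly by how often it stops when harm is present. This rule uses the threshold normally used to limit false claims of a difference, and applies it to 10 treated patients. That keeps false stops rare but makes wrongly continuing likely.

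The look comes after 10 of the 15 HOPE patients (two thirds) have been treated. If a non-significant result were taken as reassurance, it would be reassurance that the data cannot give.

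The trigger also conflicts with the endpoint. A patient who has not yet had dialysis cannot be classed as free of DGF until day 7. If the analysis is run when the tenth patient has just been treated, that patient, and any other transplanted within the preceding week, can only be missing or provisionally DGF-free. Provisional classification pushes the result towards continuing, and one patient can decide a threshold such as 7 of 10.

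**Working it through.** **Inputs from the article:** 10 HOPE patients at the look; 1:2 matching, hence 20 controls at that point, or 30 if the whole control group is used; chi-squared test, P<.05, stopping only if the HOPE rate is the higher one.

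**Assumptions:** control DGF rate 20–50%; true excess under HOPE of 20, 30 or 40 percentage points; the two groups treated as independent binomial samples. The article states no operating characteristic, so there is no figure of its own to reproduce.

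**Step 1: where the threshold lies.** With *a* of 10 HOPE and *c* of 20 control patients having DGF, let p = (a + c)/30 and z = (a/10 − c/20) / √[p(1 − p)(1/10 + 1/20)]. The uncorrected two-sided test stops when z > 1.96. Take c = 6 (30%):

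- a = 6: p = 12/30 = 0.400; z = 0.30/√(0.240 × 0.15) = 0.30/0.190 = 1.58; P = 0.11; continue.
- a = 7: p = 13/30 = 0.433; z = 0.40/√(0.2456 × 0.15) = 0.40/0.192 = 2.08; P = 0.037; stop.

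So at 6/20 in controls, 7 of 10 HOPE patients must have DGF (8 of 10 with continuity correction or Fisher's exact test). At 4/20 and 8/20 the uncorrected thresholds are 6 and 8 of 10.

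**Step 2: adequacy of the test.** The smaller expected count in the HOPE row is 10 × min(p, 1 − p), which never exceeds 5. The chi-squared approximation is therefore doubtful at every possible DGF rate.

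**Step 3: probability of stopping.** Pr(stop) = Σ Bin(a; 10, p_H) × Bin(c; 20, p_C), summed over all tables (a, c) that meet the criterion. Two-sided, uncorrected, 10 against 20:

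| Control DGF | no excess | +20 points | +30 points | +40 points |
|---|---|---|---|---|
| 20% | 2.7% | 22.5% | 40.8% | 61.1% |
| 30% | 2.9% | 19.8% | 36.6% | 57.5% |
| 40% | 2.7% | 18.3% | 35.1% | 57.6% |
| 50% | 2.6% | 17.3% | 34.7% | 60.9% |

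**Step 4: other readings of the unstated details** (range over control rates of 20–50%):

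| Version of the test | +20 points | +30 points |
|---|---|---|
| Two-sided, uncorrected, 20 controls | 17–23% | 35–41% |
| Two-sided, continuity-corrected, 20 controls | 9–14% | 21–28% |
| One-sided, uncorrected, 20 controls | 27–34% | 47–54% |
| Two-sided, uncorrected, 30 controls | 20–26% | 40–46% |
| One-sided, uncorrected, 30 controls | 32–36% | 55–57% |

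Every version misses a 20-point excess in roughly two thirds of trials or more. The two-sided versions also miss a 30-point excess more often than not. Read one-sided, the chance of stopping at 30 points is about even.

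**Step 5: an example alternative.** Stop if the posterior probability that the HOPE DGF rate exceeds the control rate is above 0.90, with flat Beta(1,1) priors. The same enumeration with 20 controls gives a stop at 6/10 against 6/20, detection of 36–47% at +20 points and 57–67% at +30 points, and a false-stop rate of about 8–11%.

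**The case against.** The strongest reply is that 10 patients cannot give high power whatever the rule. The article presents the trial as a small, nonrandomised pilot, and the example boundary also misses most 20-point excesses. Most of its gain comes from accepting more false stops, which is a matter of preference. This stands: the pilot's size is not the error, and no boundary at this size makes the look sensitive. What remains is that conventional significance was made the only trial-level trigger, without any statement of what it can detect.

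A reader might infer that the rule gives no protection, or that it would usually miss a doubling of DGF. The documents do not support either. No control rate is given, and the answer depends on it: with 20 controls and the two-sided uncorrected test, a doubling is caught in 22.5% of trials from 20%, 37% from 30%, and 58% from 40%. Nor can the test be called two-sided as a fact, since the article says only that the rate must be significantly higher. The article also does not say that a non-significant look will be read as proof of safety.

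The efficacy label is a slip. The section heading and the direction of the criterion leave no doubt that harm is meant.

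On timing, a sensible team would wait for the tenth patient's DGF status, so the practical delay is about a week. The printed trigger does not say so, and a clause would settle it.

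**Conclusion.** The concern holds in limited form. The only trial-level stopping rule in the article is insensitive to moderate harm: about 17–23% detection of a 20-point DGF excess and 35–41% of a 30-point excess (two-sided, uncorrected, 10 against 20), with a false-stop rate near 3%. For excesses of 20 points the conclusion is the same under every reading of sidedness, correction and control number that was examined; for 30 points it is the same under the two-sided readings. It does not extend to very large harm, where an excess of 40 points is caught in somewhat more than half of trials. These figures rest on assumed control rates of 20–50% and on independent binomial sampling.

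The mismatch between trigger and endpoint needs no assumption; it follows from the two sections read together. The plan should be changed on both counts, but neither undermines the pilot as such. The label is a wording correction only.

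**What to change.** 1. Trigger the interim analysis when the tenth HOPE recipient has completed day-7 DGF ascertainment. Cost: one clause and about a week's wait.
2. Replace the chi-squared P<.05 criterion with a one-sided harm boundary fixed in advance and computed by an exact or Bayesian method. State how many controls enter, and give its probability of stopping with no excess and with several sizes of excess. The posterior-probability rule above 0.90 is one example; the sponsor should choose the threshold. Cost: a few lines of code, no extra patients or data, and more false stops (about 8–11% instead of about 3% for that example).
3. State in the plan that failing to cross the boundary is not evidence of safety.
4. Change the label from efficacy to safety. No cost.

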### Ethics

The present trial will be carried out in compliance with the current version of the Declaration of Helsinki, good clinical practice guidelines (International Conference on Harmonization-Good Clinical Practice [ICH-GCP]), and all national legal and regulatory requirements. The institutional review board of the University RWTH Aachen has approved the study protocol, including consent form and patient information leaflet (EK 184/17). Members of the study team have completed a course in good clinical practice as certified by the German Medical Chamber.

### Ischemia-Reperfusion Injury and Inflammation

IRI is an inevitable event in organ transplantation. Reduction of oxygen delivery because of blood flow interruption leads to anaerobic metabolism and the production of oxygen-free radicals and oxidative stress as a respiratory burst at the onset of reperfusion. IRI plays a key role in DGF and primary graft nonfunction following kidney transplantation, depending on initial organ quality [8,9,24,25]. To detect the effects of HOPE on IRI, the kidney tissue, blood, and perfusate samples obtained in this study will be used to quantify several innovative parameters of inflammation (eg, interleukins, tumor necrosis factor-alpha), kidney injury (Cytatin-C, NGAL, etc) energy- (ATP levels) [11,26], and redox-threshold (Hemoxygenase-1, Malondialdehyde) [12,27]. Luminometry, Spectrophotometry, Luminex-assay, Enzyme-linked immunosorbent assay (ELISA), Reverse transcriptase polymerase chain reaction (RT-PCR) and Western blot will be used for these analyses. Proteomics and metabolomics analysis will be performed on kidney tissue samples to potentially identify early mediators of HOPE-mediated organ protection.

## Results

Results of this trial will be presented at national and international scientific meetings and published in international peer-reviewed medical journals. The trial was funded in the third quarter of 2017. Patient enrollment is currently ongoing, and the first results are expected in the first quarter of 2020.

## Discussion

Allogenic kidney transplantation has evolved as the mainstay of treatment for end-stage renal disease [3,28]. The decreasing availability of quality organs for transplantation has resulted in substantial organ shortage, and as such kidney donor allografts that would have previously been deemed unsuitable for transplantation have become an essential organ pool of ECD-allografts that are now routinely being transplanted on a global scale. However, the use of ECD allografts is associated with IRI and a higher incidence of primary graft nonfunction or DGF [5]. The restoration of blood flow after cold and warm ischemia leads to paradox via massive release of reactive oxygen species, cytokines, chemokines, and activation of leukocytes [29]. Although machine perfusion in kidney transplantation was explored in the 1970’s, it has not been widely used over the last few decades. Due to technical improvements and the addition of oxygen during machine perfusion, HOPE has evolved into a promising novel tool in organ preservation [11,12]. The superiority of HOPE over nonoxygenated cold machine perfusion and conventional cold storage was recently demonstrated in some preclinical experiments as well as in clinical trials using HOPE in donation after cardiac death liver transplantation [11,12,15]. A recent kidney transplantation rodent model in vivo study by Kron et al compared conventional cold storage, normothermic oxygenated blood perfusion, HOPE, and hypothermic deoxygenated perfusion using nitrogenated perfusate, and demonstrated superior effects of HOPE on macrophage activation, endothelium activation, tubular damage, and graft function as compared to other preservation methods [11].

We identified four active clinical trials exploring the effects of HOPE in kidney transplantation. In a pilot study by Ravaoili et al, 20 subjects were recruited to receive either HOPE-treated ECD-kidney or ECD-liver allografts. Whether the organs used were donated after cardiac death or donated after brain death remains unclear (NCT03031067; Table 1). One trial (NCT02621281) is a large multi-center RCT investigating HOPE in donated after cardiac death kidney transplantation, including ECD and nonECD allografts in a large Chinese cohort. Two relevant trials of the Consortium for Organ Preservation in Europe are recruiting in a large collective of patients. The Cold oxygenated machine preservation of aged renal donation after cardiovascular death transplants (COMPARE) trial (ISRCTN32967929), initiated at the University Hospital Leuven, Belgium, included a total of 102 transplanted donated after cardiac death kidney pairs that are being used to discover whether continuous oxygenated machine perfusion is superior to nonoxygenated machine perfusion. The COMPARE trial has a considerably different design compared to our study, with a logistically complex perfusion concept involving the transport of the machines to the retrieval center and applying continuous HOPE. Preimplantation oxygenated hypothermic machine perfusion reconditioning after cold storage (COPE-POMP) (ISRCTN63852508), initiated from the University Hospital of Essen, Germany, is currently ongoing and involves randomizing ECD allografts to end-ischemic preimplantation HOPE or to conventional cold storage.

Although we have designed our trial carefully, nonrandomization of the study groups and nonblinding of the transplant team, as well as matching with a historical group, are limitations of the present study. Nevertheless, conclusive clinical data about end-ischemic HOPE in human kidney transplantation are still missing and larger multi-center studies on this topic are currently underway. Therefore, it seems plausible to conduct this trial as a pilot study with a focus on short-term outcomes as well as translational research aspects of HOPE in ECD-kidney transplantation.

The present trial, nevertheless, possesses some specific strengths in that it focuses on patients solely receiving ECD-allografts, a population in which we anticipate the best cost/benefit ratio from the utilization of HOPE. Kidney transplant outcomes stem from a combination of various factors. Our matching criteria have been carefully selected based on previous clinical evidence to include both donor and recipient factors, which have a key role to play in posttransplant outcome [30,31]. Regarding translational research and sample collection, our study design as a single center prospective trial may also be beneficial. Samples will be obtained according to our study protocols and by the same study members throughout the whole study period. The results of the translational part of this study may deliver novel insights into the underlying subcellular effects of HOPE in human kidney transplantation.

**Table 1 table1:** Active prospective clinical trials on HOPE (hypothermic oxygenated machine perfusion) in kidney transplants (as assessed on clinicaltrials.gov and isrctn.com on February 27, 2019).

Trial number	Study center	Study type	Enrollment	Donor group	MP^a^ point of time
NCT03378817 (Present trial)	University Hospital Aachen, Aachen, Germany	CS^b^	15	ECD^c^-donated after brain death	End-ischemic
NCT03031067	University of Bologna, Bologna, Italy	CS	10	ECD (donated after brain or cardiac death unclear)	Unclear
NCT02621281	First Affiliated Hospital Xi’an Jiaotong University, Xi’an, Shaanxi, China	RCT^d^	400	donated after cardiac death	Immediately after retrieval
ISRCTN32967929	University of Leuven, Leuven, Belgium	RCT	210	donated after cardiac death	Immediately after retrieval
ISRCTN63852508	University Clinic Essen, Essen, Germany	RCT	262	ECD-donated after brain death	End-ischemic

^a^MP: machine perfusion.

^b^CS: cohort study.

^c^ECD: extended criteria donor.

^d^RCT: randomized controlled trial.

## Abbreviations

ATP: adenosine triphosphate
CIT: cold ischemic time
COMPARE: cold oxygenated machine preservation of aged renal donation after cardiovascular death transplants
COPE-POMP: preimplantation oxygenated hypothermic machine perfusion reconditioning after cold storage
CRF: case report file
DGF: delayed graft function
ECD: extended criteria donor
eGFR: estimated glomerular filtration rate
ELISA: enzyme-linked immunosorbent assay
ESRD: end-stage renal disease
HOPE: hypothermic oxygenated machine perfusion
HTK: histidine-tryptophan-ketoglutarate
ICH-GCP: International Conference on Harmonization-Good Clinical Practice
IRI: ischemia-reperfusion Injury
kPa: kilopascal
MPS: machine perfusion solution
NGAL: neutrophil gelatinase-associated lipocalin
O2: oxygen
pO2: partial pressure of oxygen
RWTH: Rheinisch-Westfälische Technische Hochschule
